**Methods:**

This study will comprise a randomized, controlled, single-blind clinical trial concerning women with breast cancer-related lymphedema undergoing treatment at a public cancer treatment reference hospital in the city of Rio de Janeiro, Brazil. The intervention will be carried out by adapting self-dressing versus the standard treatment of compressive bandaging (phase 1) and compressive mesh (phase 2). Both groups will be assessed at the beginning and end of intensive treatment and followed up for up to 12 months to evaluate immediate and late outcomes. Assessments will be carried out by physical upper limb examination (inspection, palpation, volume, dynamometry, and thermography) and questionnaires application to assess patient’s quality of life pertaining to the health, functionality, and symptoms of the affected upper limb, as well adverse effects and adherence to treatment. Data will be analyzed descriptively and analytically through univariate and multiple linear regressions. *P* values < 0.05 will be considered statistically significant.

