### Sample size {14}

Considering the benefits of complex physical therapy when there is a percentage reduction in excess limb volume of 22% to 73% [21], and, for the use of compressive therapy, an estimated response of 33.5% reduction in excess limb volume [22], we stipulated a 35% variation in treatment response between the groups, with an estimated treatment response of 45% in the control group (standard care) and 80% in the intervention group. The sample size was calculated considering a confidence level of 95% with a study power of 80% and a 1:1:1:1 ratio between the intervention groups. Thus, a total population of 120 patients (30 in each group) will be required. To cover possible losses to follow-up and treatment interruption, a total of 20% will be added to the number of participants Therefore, the total sample to be included in this study will be of 144 women (36 in each group).

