## Statistical methods

### Statistical methods for primary and secondary outcomes {20a}

A descriptive analysis of the sociodemographic and clinical characteristics of the study population will be carried out through the distribution of absolute and relative frequencies for categorical variables and central tendency and dispersion measures for continuous variables. The thermographic analysis will be obtained by the average difference in temperatures of one limb in relation to the other and a cut-off point will be established. Data normality will be calculated using the Kolmogorov–Smirnov test. Group comparisons will be done by using Student’s *t* test or Wilcoxon test for continuous variables and chi-square test for categorical variables. The effect size of the mean outcomes will be calculated using Glass’s delta (considering 0.2 as small, 0.5 as medium, and 0.8 as large effects) [23]. Associations between the variables of interest and the outcome will be performed using univariate linear regression. Variables presenting *p* ≤ 0.20 will be included in the multiple linear regression model employing the stepwise forward method, and those with *p* < 0.05 or with clinical relevance will be maintained in the adjusted model. A significance level of 5% will be accepted, at a confidence interval of 95%. Statistical tests will be performed using the SPSS version 23.0 software.

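### The adjusted treatment effect comes from a p ≤ 0.20 screen and forward stepwise regression that neither forces in the randomised arm nor fixes the covariates

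*Protocol article*

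**What the plan says.** The section Statistical methods for primary and secondary outcomes {20a} sets out two layers of analysis.

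- **Unadjusted:** groups are compared by t or Wilcoxon test for continuous variables and by chi-square test for categorical ones.
- **Regression:** variables of interest are related to the outcome by univariate linear regression. Those with p ≤ 0.20 "will be included in the multiple linear regression model employing the stepwise forward method". Variables with p < 0.05 or "with clinical relevance will be maintained in the adjusted model".

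The abstract gives the regression layer prominence: "Data will be analyzed descriptively and analytically through univariate and multiple linear regressions".

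Trial design {8} describes a 1:1 randomised superiority trial. Sample size {14} rests on a binary response, "with an estimated treatment response of 45% in the control group (standard care) and 80% in the intervention group", and concludes that "a total population of 120 patients (30 in each group) will be required". The Primary outcome section defines response by a 10% change in limb volume and also defines a percentage reduction from initial volume.

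**The concern.** In a randomised comparison the arm is the question, so it belongs in every model that claims to estimate the treatment effect. The written rule treats it as one candidate among many. It can fail the screen or fail to enter, and the adjusted effect is then not reported. If it enters on its p value, it is seen mainly when chance has made it look large. The clinical-relevance clause allows the arm to be kept but does not require it. Because the clause is undefined, the decision can be taken after the results are known.

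Selecting the other covariates by p value also makes the standard error of the arm effect too small. An unadjusted and a selected adjusted result will then stand side by side, with no statement of which one carries the conclusion. At about 30 women per arm, these effects are not negligible.

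**Working it through.** **1. Which comparison is powered.** Inputs from Sample size {14}: 45% v 80%, 80% power, 95% confidence (two-sided assumed). With a pooled proportion of 0.625:

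n = [1.960·√(2·0.625·0.375) + 0.842·√(0.45·0.55 + 0.80·0.20)]² / 0.35² = (1.342 + 0.537)² / 0.1225 = 28.8, so 29 per group.

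The stated 30 is reproduced. Power at 30 per group is 81.6%, both by formula and by exact enumeration of the uncorrected chi-square test. The trial is therefore powered for a two-proportion comparison, and the listed chi-square test fits it.

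**2. Why the arm drops out.** At 30 per arm the standard error of a mean difference is √(2/30) = 0.258 SD.

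- The arm fails the p ≤ 0.20 screen (noncentral t, 58 df) with probability 54% at a true 0.3 SD, 26% at 0.5 SD, 6.8% at 0.72 SD and 0.7% at 0.97 SD.
- To be retained on its p value it must also reach p < 0.05. If the other covariates carry no information, that requires an estimate beyond 2.002 × 0.258 = 0.52 SD. A true effect of 0.5 SD is then kept only when it is overestimated.
- The design effect on this scale, assuming a normal latent outcome, is z(0.80) − z(0.45) = 0.842 + 0.126 = 0.97 SD.

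**3. Simulating the p-value rules.** None of these inputs is in the documents. There are 30 per arm and a normal outcome, with 1,500 to 5,000 runs per scenario.

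- Setup A: baseline with r = 0.5, three weak covariates (r = 0.2) and nine irrelevant ones.
- Setup B: 10 or 20 independent covariates, three with slope 0 or 0.4, residual SD 1.

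| True effect | Arm absent | Mean estimate when kept |
|---|---|---|
| 0.3 SD (B) | 79–83% | 0.64–0.69 |
| 0.5 SD (A and B) | about 45–60% | 0.64–0.76 |
| 0.72–0.74 SD (A and B) | 12–31% | 0.77–0.84 |
| 0.97 SD (A) | about 1–2% | 0.95 |
| 0.97 SD (B, no informative covariate) | 4–5% | 0.99 |

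The last row agrees with a direct calculation: one minus the t-test power at 0.97 SD is 4.2%.

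**4. Error rates with no true effect.**

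- Arm forced in, covariates selected: type I error 6.4–6.8%, 95% CI coverage 93.2–93.6%.
- Arm and one prespecified covariate: type I error 5.2–5.4%.
- Either the unadjusted or the selected-model result may be claimed: 6.7–9.1%.

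Simulation error is about √(0.05·0.95/5000) = 0.3 percentage points at 5,000 runs, and 0.5 points at 2,000.

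**5. Precision from baseline adjustment.** The standard error shrinks by 1 − √(1 − r²): 13% at r = 0.5, 2% at r = 0.2 and nothing at r = 0. The documents give no correlation.

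**The case against.** The section gives group comparisons their own sentence and introduces the regression for associations with the outcome. The arm cannot drop out of a t test or a chi-square test. The clinical-relevance clause also lets the analyst keep the arm, and at the effect the trial was designed for the p-value rules would seldom remove it. All of this stands, and it limits the point to the adjusted analysis. It does not rescue that analysis: a rule that permits the arm to be kept does not require it, and the abstract presents the regressions as the analysis.

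Three stronger readings are tempting, and the documents do not support them.

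- *No planned test matches the powered endpoint.* The only regression named is linear, but the chi-square test is listed and fits the responder rate. What is missing is a sentence tying it to the primary outcome.
- *The plan ignores baseline volume.* The percentage reduction in the Primary outcome section is already calculated from initial volume. Further gain from adjustment depends on an unknown correlation.
- *The primary analysis should become an ANCOVA of excess volume.* That would replace the powered responder endpoint. It would also need follow-up measurements of the opposite limb, which the article does not state.

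An unseen analysis plan may add detail. The screen and the stepwise rule, however, are stated here and not left open.

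**Conclusion.** The point holds for the adjusted analysis. As written, the rule can omit the randomised arm, overstate its effect when it is kept, and leave the choice to judgement after the data are seen. The size depends on the true effect: serious around 0.5 SD or below, moderate near 0.7 SD, and small at the design-equivalent 0.97 SD. Type I inflation of the adjusted test alone is modest. The larger harms are the missing or selectively reported estimate and the free choice between two results. The absence and inflation figures model the p-value rules alone and rest on assumed covariate numbers and strengths. The defect in the rule does not depend on them.

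**What to change.** For each phase:

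1. Name the responder comparison by chi-square test as the primary analysis, matching Sample size {14}. The sample size does not change.
2. For adjusted analyses, delete the p ≤ 0.20 screen, the stepwise entry and the retention rule. Always include the randomised arm and prespecify baseline affected-limb volume as covariate.
3. Use a linear model (ANCOVA) for 30-day volume or percentage change. If the responder outcome is adjusted, use a logistic or risk-difference model.
4. Report the arm effect with its 95% CI whatever its p value, and state that adjusted results support the primary analysis and do not replace it.

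The cost is wording. Affected-limb volume is already measured before treatment and at 30 days, so no new patients or measurements are needed. The change should be dated before the 30-day data are analysed by arm.

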### Interim analyses {21b}

An initial analysis is planned with the data obtained in the 30-day evaluation after study inclusion of each volunteer for both groups, with the statistical analysis carried out by the blind researcher according to the statistical planning.

### Methods for additional analyses (e.g., subgroup analyses) {20b}

There is no plan for subgroup analyses.

### Methods in analysis to handle protocol non-adherence and any statistical methods to handle missing data {20c}

Outcome assessments will be performed by intention to treat and protocol adherence will be verified.

### Plans to give access to the full protocol, participant level-data and statistical code {31c}

The collected and stored data analyzed in this study may be made available by the main investigator in case of formal request with plausible justification for its use.

## Oversight and monitoring

### Composition of the coordinating center and trial steering committee {5d}

This is a study developed in a single location and with few researchers involved. Therefore, no judging committee is included. However, team support is available, as follows: the principal investigator assumes the supervision of the judging committee and technical responsibility for the physiotherapeutic conducts applied to the study participants and is also responsible in case of adverse effects; the study project coordinator carries out test registrations, coordinates technical visits, guarantees the reports, and assists in data organization and protection; physiotherapist 1 performs reassessments and organizes and protects data quality; physiotherapist 2 identifies potential recruits, signals the sector’s physiotherapy team, receives patients, informs the protocol, advises on the informed consent form, performs evaluations, and ensures participant follow-up according to the applied protocol.

### Composition of the data monitoring committee, its role and reporting structure {21a}

A data monitoring committee was not formed for this study. This decision was made based on the absence of serious adverse effects by the applied treatments, both in the experimental treatment and the control, which is the institution’s standard. In any case, control and notifications by the research physiotherapists involved in the study of possible adverse effects and undesirable symptoms reported by the volunteers will be performed. If unwanted effects resulting from the treatment are observed, the participant will withdraw from the study and the institutional routine will be conducted, depending on the situation, and all necessary medical support will be provided.

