### Criteria for discontinuing or modifying allocated interventions {11b}

Treatment suspension before the proposed period will be implemented when side effects occur, such as allergic reactions or poor adaptation to the employed material, as well as limb volume increases greater than 10% of the initial volume, affected upper limb infection and decompensated systemic blood pressure. In the case of any other unforeseen changes, the patient will be evaluated by the health team and any necessary procedures will be adopted.

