#### Adverse events

Adverse events will be verified during the first and second treatment phase through therapeutic diary reports and notes regarding the occurrence and intensity of the following symptoms: contact dermatitis, skin infection, uncompensated arterial hypertension, and upper limb volume worsening by 10% of the initial volume, among other unforeseen effects. In addition, all participants will also be provided with a telephone contact that will serve as a communication channel between participants and therapists for reporting adverse events, unpleasant symptoms, and/or questions about the lymphedema treatment, as well as any guidance, when relevant.

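### The data-monitoring section withdraws participants with unwanted effects from the study, which conflicts with suspension-only wording, 12-month follow-up and intention to treat elsewhere

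*Protocol article*

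**What the plan says.** Several parts of the protocol bear on what happens to a participant who does not tolerate the allocated compression.

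- **Data monitoring committee {21a}:** "If unwanted effects resulting from the treatment are observed, the participant will withdraw from the study", after which the institution's routine care applies. The rule has no qualification and refers to the study, not the treatment.
- **Discontinuing or modifying interventions {11b}:** "Treatment suspension before the proposed period will be implemented when side effects occur". The triggers include "limb volume increases greater than 10% of the initial volume, affected upper limb infection and decompensated systemic blood pressure". Nothing is said about leaving the study. Adverse event reporting and harms {22} repeats the suspension rule for largely the same events.
- **Adverse events (secondary outcomes):** the events to be recorded are "contact dermatitis, skin infection, uncompensated arterial hypertension, and upper limb volume worsening by 10% of the initial volume, among other unforeseen effects". Section {22} gives the same list.
- **Post-trial care {30}:** a rise of over 10% seen at the 30-day reassessment, with function or quality of life compromised, leads to referral to standard treatment. Leaving the study is not mentioned.
- **Interventions, end of the Group D text:** participants in each group are reassessed at 6 and 12 months.
- **Primary outcome:** phase 1 success is a volume reduction of over 10%. Phase 2 success is maintenance or a variation of up to 10%.
- **Analysis {20c}:** "Outcome assessments will be performed by intention to treat and protocol adherence will be verified".
- **Sample size {14}:** the 20% addition is made "To cover possible losses to follow-up and treatment interruption".

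**The concern.** Intention to treat needs outcomes from everyone randomised, including those who stopped the allocated treatment. A rule that ends study participation when an unwanted effect appears works against this, because the volume and questionnaire data that would have followed are never collected.

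The loss would not be random. It depends on tolerance of the material, which may differ between wrap, bandage and mesh. It may also depend on limb volume itself: 10% worsening is listed as an adverse event, and a volume rise is a reason for suspension. In phase 2 a rise above 10% is treatment failure; in phase 1 it is one part of failure. If more such participants leave one arm than the other, the comparison is biased, and the remaining data cannot show in which direction.

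The sample-size section points the same way. It groups treatment interruption with loss to follow-up, although under intention to treat a participant who interrupts treatment is not lost.

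**Working it through.** **1. Can the statements hold together?** Take a participant who develops contact dermatitis on day 10.

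| Section | Consequence |
|---|---|
| {11b}, {22} | Treatment suspended |
| {21a} | Leaves the study; institutional routine |
| Interventions | Reassessed at 6 and 12 months |
| {20c} | Analysed by intention to treat |

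The second row excludes the third and leaves the fourth without day-30 or later data for this person.

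**2. Does the rule reach the primary outcome?** Section {21a} does not name a volume rise. The link is indirect: worsening by 10% is on the adverse-event lists, and "limb volume increases greater than 10% of the initial volume" is among the suspension triggers in {11b}. The rule can therefore be read to cover it.

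**3. When would data be lost?** In phase 2 the early face-to-face evaluations are on days 1 and 30, and day 7 is a phone call. Unless an extra visit is arranged, a rise above 10% is first measured on day 30 and is recorded there. In phase 1 a rise could be seen on day 7. Intolerance can appear at any time in either phase. The exposed data are thus day-30 outcomes of those withdrawn earlier, and 6- and 12-month outcomes of anyone withdrawn.

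**4. The plan's own sample size.** Inputs from {14}: 45% and 80%, 95% confidence (taken as two-sided 5%), 80% power. Pooled two-proportion formula, mean rate 0.625:

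n = [1.960·√(2·0.625·0.375) + 0.842·√(0.45·0.55 + 0.80·0.20)]² / 0.35² = 28.8, so 29 per group.

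The stated 30 is reproduced to within one patient (power 81.6%), and 30 × 1.20 = 36. With all 36 per group measured, power is 88.3%.

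**5. Illustration of bias within the plan's allowance.** Assume 36 randomised per arm, true rates 45% and 80%, and six failures lost unmeasured and dropped from the denominator, leaving the 30 that the plan requires. The number six and the premise that all six are failures are assumptions; the protocol gives no withdrawal rate.

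- Control: 36 × 0.45 = 16.2 successes; 16.2/30 = 54%.
- Intervention: 36 × 0.80 = 28.8 successes; 28.8/30 = 96%.

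| Six failures lost in | Control | Intervention | Difference |
|---|---|---|---|
| neither arm | 45% | 80% | 35 points |
| control only | 54% | 80% | 26 points |
| intervention only | 45% | 96% | 51 points |
| both arms | 54% | 96% | 42 points |

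If the true rate were 45% in both arms, losing six failures from one arm would give 54% against 45%, a 9-point difference where none exists.

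**6. Equal shares.** If the same share w of failures is lost in both arms, the observed rate is p/(1 − w(1 − p)). At w = 0.25 this gives 0.45/0.8625 = 52.2% and 0.80/0.95 = 84.2%, a difference of 32.0 points. At w = 0.5 it gives 62.1% and 88.9%, 26.8 points, but that removes 0.5 × 55% = 27.5% of the control arm, more than the plan's 20% allowance. Larger shares are not a realistic guide.

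**The case against.** The strongest reply is that {21a} concerns the monitoring committee, and that the sections governing side effects and volume increase prescribe suspension or referral only. On that reading the withdrawal sentence is loose wording. This may be what was meant, but the sentence is categorical, and staff who follow it would end follow-up.

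A reader might go further and infer that participants whose volume rises by more than 10% are removed as failures and that the tests are run only on those who tolerated and benefited. The documents do not support this:

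- {21a} does not name the volume rise.
- That rise defines failure only in phase 2. In phase 1 a participant with a 5% reduction also fails, and no rule withdraws her for that.
- A rise must be measured to be known, and one found on day 30 is already recorded.
- No section excludes withdrawn participants from analysis, and {20c} says the opposite in principle.
- Section {14} enlarges the sample; it does not replace anyone.

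It is also fair to say that the handling of missing values may sit in an analysis plan that is not shown, so its absence here is no fault. That does not answer the point, because an analysis plan can handle missing volumes but cannot recover volumes that the protocol told staff not to collect.

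**Conclusion.** The concern holds as a contradiction within the protocol with a real risk of bias. Withdrawal from the study in {21a} cannot be reconciled with suspension of treatment in {11b} and {22}, reassessment at 6 and 12 months, and intention to treat in {20c}. Followed as written, it loses outcomes for reasons related to tolerance and possibly to volume.

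The size depends on how many participants withdraw, from which arm, and what their outcomes would have been, none of which the protocol gives. Under the stated assumption of six unmeasured failures, a true 35-point difference could appear as anything from 26 to 51 points. These figures show what the plan's own allowance would permit; they are not a forecast. They apply to outcomes not yet recorded at withdrawal and not to a volume rise first found at the day-30 visit.

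**What to change.** Reconcile {11b}, {14}, {20c}, {21a}, {22} and {30}. Which events lead to suspension or referral, and at what threshold, is for the sponsor to decide; nothing here requires a change to those criteria.

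1. In {21a}, state that stopping the allocated compression does not end study participation unless the participant withdraws consent.
2. Keep the scheduled day-30, 6-month and 12-month assessments for those who have stopped.
3. In {20c}, state that all measured volumes are analysed by randomised group, whether or not treatment was stopped.
4. In {14}, limit the 20% allowance to loss of outcome data and do not count treatment interruption as a loss.
5. Add a sensitivity analysis that counts missing binary outcomes as failures. Scoring intolerance itself as failure in the main analysis is not recommended, because it would change the volume-based endpoint.

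The cost is wording, plus the effort of following participants who have stopped treatment, at visits already scheduled. The change cannot recover data from participants already withdrawn: 115 had been included by 24 May 2023. Report those withdrawals by arm with reasons.

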#### Group D: Standard compressive mesh intervention

This group will receive the standard upper limb volume maintenance treatment employing a compressive mesh that provides 30 to 40 mmHg of pressure and has an elastic Velcro strap for fixation that will be adapted according to ideal size indications following affected upper limb perimetry measurements. The compressive mesh must be continuously used, removing the mesh only for bathing and night sleeping. After 7 days of adaptation, the research team will contact the patients by phone to monitor possible adverse events and assess the need for face-to-face consultations. Outpatient follow-up and evaluations in face-to-face consultations will take place on the 1st and 30th day after adaptation.

Participants in each intervention group will be followed and reassessed 6 and 12 months after study enrollment to verify long-term outcome measures. At the end of this period, the standard compressive mesh will be adapted and provided free of charge according to the applied institutional routine.

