## Data collection and management

### Plans for assessment and collection of outcomes {18a}

The data collection will take place through interviews, physical examinations, and medical record analyses. All data will be collected by experienced physiotherapists. The interviews will consist of semi-structured questionnaires produced by the researchers, in addition to questionnaires validated for the Brazilian population. Regarding the physical examination, the volume of the upper limb with lymphedema will be evaluated using perimetry, tissue characteristics using thermography, and muscle strength will be evaluated using dynamometry. These assessment resources will be used for all participants included in the study and performed before and after the initial 30 days of treatment and during follow-up (6 and 12 months). Data regarding oncological treatment and lymphedema treatment history will be obtained from physical and electronic medical records.

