### Plans to promote participant retention and complete follow-up {18b}

Study participants will receive the necessary information to understand the evaluation flow and the importance of completing the follow-up, comprising a teleconsultation within 7 days after study inclusion (at the beginning of the treatment) and face-to-face returns for reassessment in 30 days, 6 months, and 1 year. Any study participant can withdraw and leave the study at any time without necessarily explaining the reasons for withdrawal. Thus, whenever problems contacting the participant by phone (call or text message) arise, the institution will ask the institution to send a telegram to the participant’s registered address, instructing them to contact the physiotherapy sector to schedule their appointment.

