### Adverse event reporting and harms {22}

The occurrence and intensity of the following symptoms will be verified during the first and second treatment phases through reports and notes made in the therapeutic diary: contact dermatitis, skin infection, uncompensated arterial hypertension, and worsening of upper limb volume by 10% of the initial volume, among other unforeseen effects. In addition, all participants will also be provided with a telephone contact that will serve as a communication channel between participants and therapists for reporting adverse events, unpleasant symptoms, questions about lymphedema treatment, and guidance, when relevant. Treatment suspension before the proposed period will take place when side effects are observed, such as allergic reaction or poor adaptation to the applied material, increase in upper limb volume by 10% of the initial volume, affected upper limb infection, and decompensated blood pressure. If any other unforeseen change occurs, the case will be evaluated by the health team and the necessary procedures will be adopted.

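### The {21a} rule that takes women with unwanted treatment effects out of the study conflicts with treatment-only suspension, 12-month follow-up of everyone and intention to treat

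*Protocol article*

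**What the plan says.** All references are to the protocol article.

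- **Data monitoring committee {21a}:** "If unwanted effects resulting from the treatment are observed, the participant will withdraw from the study and the institutional routine will be conducted". What triggers the exit is an observed effect, not the woman's decision.
- **Criteria for discontinuing or modifying allocated interventions {11b}:** "Treatment suspension before the proposed period will be implemented when side effects occur". The listed reasons are allergy, poor adaptation, a volume rise above 10%, limb infection and decompensated blood pressure. Adverse event reporting and harms {22} repeats essentially the same list with the same consequence. Neither section mentions leaving the study.
- **Follow-up, at the end of the phase 2 interventions:** "Participants in each intervention group will be followed and reassessed 6 and 12 months after study enrollment".
- **Plans for assessment {18a}:** the measurements apply to "all participants included in the study and performed before and after the initial 30 days of treatment and during follow-up (6 and 12 months").
- **Analysis {20c}:** "Outcome assessments will be performed by intention to treat".
- **Retention {18b}:** "Any study participant can withdraw and leave the study at any time without necessarily explaining the reasons for withdrawal". This is the ordinary voluntary exit.
- **Post-trial care {30}:** a rise of more than 10% found at day 30 that compromises function or quality of life leads to referral to the institution's standard treatment. No exit from the study is stated.

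**The concern.** For the same kind of event the document gives two instructions that cannot both be followed. Under {11b} and {22} the physiotherapist stops the garment or bandage and the woman is still measured. Under {21a} her participation ends. Nothing in the document says that women withdrawn under {21a} are still measured.

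The events concerned are tied to treatment and, in part, to the primary outcome. Volume worsening by 10% is a listed adverse event, and in phase 2 a change beyond 10% is a failure of the primary outcome. If such women leave, their missing volumes are not missing at random, and the two arms may lose different numbers of them. Intention to treat keeps a woman in her allocated arm but does not replace a volume that was never taken.

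The exposure is not confined to the late visits. Phase 1 has an evaluation at day 7, and phase 2 has a day-7 call that asks about adverse events. A woman withdrawn then would also have no day-30 volume, in either phase.

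**Working it through.** **1. The plan's own figure.** No planned number is in dispute. With 45% v 80% response, two-sided 5% and 80% power, the pooled formula gives n = [1.96·√(2·0.625·0.375) + 0.842·√(0.45·0.55 + 0.80·0.20)]² / 0.35² = 28.8, so 29 per group against 30 stated. Adding 20% gives 30 × 1.2 = 36. Power is about 88% with 36 per group and 82% with 30. The allowance therefore covers the loss of about 6 women per group in numbers. It does nothing about bias.

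**2. Model for the late phase 2 comparison.** Let q be the share failing in an arm and f the share of those failures withdrawn. If later status equals earlier status, the success seen among women still measured is

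observed success = (1 − q) / (1 − q·f).

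The document gives no phase 2 failure rate with a justification and no withdrawal share. Every q and f below is an assumption. Differences are garment minus mesh, in percentage points.

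| Failure, mesh v garment | Withdrawn, mesh v garment | Observed success, mesh | Observed success, garment | True difference | Seen |
|---|---|---|---|---|---|
| 20% v 10% | 50% v 50% | 0.80/0.90 = 88.9% | 0.90/0.95 = 94.7% | 10.0 | 5.8 |
| 20% v 10% | 25% v 75% | 0.80/0.95 = 84.2% | 0.90/0.925 = 97.3% | 10.0 | 13.1 |
| 20% v 10% | 75% v 25% | 0.80/0.85 = 94.1% | 0.90/0.975 = 92.3% | 10.0 | −1.8 |

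With 20% failure in both arms and 75% v 25% of failures withdrawn, observed success is 0.80/0.85 = 94.1% v 0.80/0.95 = 84.2%. That is a gap of 9.9 points where none exists.

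With equal withdrawal shares the difference shrinks. With unequal shares it can be inflated, reversed or created.

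**3. Early exits in phase 1.** Suppose that both arms truly have 45% response and that every woman withdrawn before day 30 would have been a non-responder. Withdrawal of 20% v 10% gives 0.45/0.80 = 56% v 0.45/0.90 = 50%, a false difference of about 6 points at day 30. Equal withdrawal gives none. These rates are again assumptions.

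**4. What the numbers can and cannot absorb.** In the first row of the table, 36 × 0.20 × 0.5 = 3.6 and 36 × 0.10 × 0.5 = 1.8 women are lost. Both are within the 6 per group allowed, yet the difference is still seen as 5.8 in place of 10.0.

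**The case against.** The best defence is that {21a} is not the operative rule. Its purpose is to explain why there is no monitoring committee, while the sections on discontinuation, harms, follow-up, assessment and analysis all point the other way. On this view, leaving the study is loose wording for leaving the study treatment, softened by the end of the sentence: "the institutional routine will be conducted, depending on the situation". This may be what the investigators intend. But the softening phrase most naturally qualifies the routine care, {18b} uses the same verb for a real departure, and staff can follow only what is written. The defence supports the correction and does not remove the conflict.

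A second objection stands in part. A reader might infer that every woman whose limb has grown by more than 10% at day 30 is removed. The document does not say so: {21a} does not name a volume rise, and {30} has its own rule for that finding, which is referral without a stated exit. Applying {21a} to these women rests on the adverse-event and harms lists and is an inference.

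A reader might also infer that the bias must pull toward no difference, that it vanishes if the arms fail equally, or that the day-30 result is safe. The first two hold only if the same share of failures leaves each arm. The third fails for anyone withdrawn before day 30.

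Missing-data methods may well be in an analysis plan that is not shown. That is no answer to a rule that stops the measurements.

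**Conclusion.** The contradiction is in the text and is worth correcting. If {21a} is applied as written, volumes go missing for reasons linked to treatment and possibly to outcome: at 6 and 12 months, and at day 30 for early exits, in both phases.

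Neither the size nor the direction of the bias can be fixed from the document. Under the assumed rates, a true 10.0-point difference is seen as anything from about −1.8 to 13.1, and a difference of 9.9 points can arise from none. These figures assume that later status follows earlier status and that withdrawal is confined to failures. There is no bias if nobody is withdrawn.

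The document does not show that any woman has in fact been lost this way, and the point does not claim it.

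**What to change.** In {21a}, replace the clause that has the participant withdraw with: *the allocated treatment will be stopped; the participant remains in the study, is measured at 30 days, 6 and 12 months unless she withdraws consent, and is analysed in her allocated arm.* Leave {11b}, {22} and {30} unchanged, including the referral criterion in {30}.

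For phase 2 women already withdrawn after a volume rise above 10%, add a sensitivity analysis that counts them as not successful at the visits they missed.

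The cost is one sentence, an instruction to the physiotherapists and one sensitivity analysis. If the change is judged substantial, the ethics committee is told and affected participants are informed, as {25} provides. No patients or visits are added, because the visits are already planned, and treatment still stops when it should.

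The benefit is limited to visits still ahead. Recruitment began in August 2021, and 115 women had been included by 24 May 2023, so some late visits had already passed. Women enrolled in the 12 months before that date still had their 12-month visit to come.
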